In order to fill the described gaps in the support system for cannabis using adolescents and young adults, our research group developed a structured, manualized group training programme "CAN Stop", which focuses on this specific target group between age 14 and 21, whose needs so far have not been adequately met by the various support system components. The first goal of the project is to provide for an evaluated, evidence-based group programme, which can be easily disseminated and which is tailored to the developmental characteristics and contexts of adolescents and young adults. We hypothesize that young cannabis users who participated at the CAN Stop group training in addition to the treatment or service usually provided in the specific help provision context (e.g. drug addiction aid and youth welfare, in-patient medical context, out-patient medical context, juvenile prisons) show lower level of cannabis intake and higher levels of cannabis abstinence-related self-efficacy after the training as opposed to young cannabis users who received the usual treatment or service. As for the implementation of the programme, we are aware of the existing subdivided and at times confusing help provision system for young cannabis users in Germany, and we believe it is inherent for the effectiveness and for the future dissemination and practicability of the programme, that it is tried out within these different help provision settings. We hypothesize, that because of their above mentioned structural and organizational characteristics, different clientele and context-specific staff will be met within these settings. That is why the programme is implemented and evaluated separately in four different settings (a) the drug addiction aid and youth welfare system, (b) the out-patient medical system, (c) the in-patient medical system and (d) prisons for juvenile offenders. This offers the possibility to check for the suitability of the programme in different settings - our second goal - and to compare its effectiveness and utility within them. Our third goal is to draw conclusions for the future implementation of the CAN Stop training in different help provision settings. Moreover, our fourth goal is to gain knowledge about the incoming clientele of the different settings with regard to their substance use patterns, severity of dependence, psychosocial adjustment, expected effects of cannabis use and family and peer relations. As for the realization of the training programme, this remains in the hand of the existing staff of the different settings. A novelty of the programme is, that no specific prerequisites are prescribed as to the professional background or existing (therapeutic) experience of the trainers. The only exception is the staffs' contact with cannabis using adolescents and young adults as part of their occupation within one of the above mentioned settings and a basic interest to realize the training. This approach may include staff from prison guards, to ex-users working in the addiction aid system to psychotherapists and medical doctors and nurses. With this approach, the introduced study not only evaluates the effectiveness of a group training programme for cannabis using adolescents and young adults (14-21) but also evaluates the instructions given to the trainers, who perform the actual training with the target group, in form of a course of instruction and a newly developed manual. The fifth goal of the project is to evaluate the CAN stop group training programme with regard to its gender-specific utility and effectiveness. Previous therapeutic approaches were evaluated with largely male samples. This may in part be due to the higher prevalences of male cannabis users, but may to some extent also lie in the fact, that previous programmes and approaches were more shaped to address males and were not equally fit to address the specific needs of female cannabis users. The CAN Stop group training was explicitly developed to meet both male and female young cannabis users' needs in that it for example also refers to accompanying internalizing problems and the importance of the dynamics of a romantic partnership with cannabis use patterns - topics which are deemed to address especially female young cannabis users.

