In a first attempt to identify suitable cooperation partners, we systematically scanned comprehensive help provision and therapy guides of Northern and Eastern Germany as well as the Internet for institutions. All identified institutions were then invited to participate at the study with an information letter and asked to fax back an attached reply form together with a questionnaire about structural and work details of the institution, such as number of incoming young cannabis users in the targeted age range and number of staff. Prior to this, a target number of cooperation partners needed to gather the subjects was calculated on the basis of a power calculation, an estimated attrition rate of 50% and under the premise that CAN Stop training groups should be composed of six to ten group participants. If feedback was not given within six weeks after letters were sent out, a study group member called to check back with the institution. An exception from this procedure was made within the setting of juvenile prisons: because their total number was rather low, their staffs were contacted directly via phone calls. The response rate varied between different settings between 57% in juvenile prisons, 10% in in-patient medical clinics, 5% in out-patient medical clinics and 5% in the youth welfare and drug addiction aid. If institutions signalled to be in contact with young cannabis users in their daily routines and were interested in study participatioin, a study group member gave a presentation of the project and invited institutions to participate at the study. In sum, we could aquire a total of 11 cooperation partners within the youth welfare and drug addiction aid, 9 cooperation partners of the out-patient medical system, 8 cooperation partners of the in-patient medical system and 3 participating prisons for juvenile offenders. Participating cooperation partners were randomly assigned to perform the CAN Stop intervention plus their usual treatment as an intervention group or to provide for control group subjects, who received the cooperation partner's previously installed treatment as usual (TAU). As for other treatments, provided by the different institutions (besides CAN Stop), cooperation partners differed in their usually provided routines depending on their specific setting. While most prisons indicated, other kinds of therapy besides CAN Stop were rather limited and merely consisted of counselling talks or conceptual work within the organizational framework of the prison, the in-patient medical system's cooperation partners of course provided many other facets of treatment - to mention both extremes of this varying continuum. Institutions, which indicated they were already participating in other structured programmes similar to CAN Stop were excluded from the study in order not to compare CAN Stop with eventually competing studies (e.g. FrED, see above).

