### Analysis

An intention-to-treat approach will be taken to analyze data. Comparisons will be made between intervention group and the TAU control group in the different settings using baseline controlled ANCOVAs with cannabis use and abstinence-oriented self-efficacy as dependent variable and cannabis use at t0 as covariate. We plan to perform nested analyses in order to handle the variance, which is shared between participants attending the same institution. There are no institutions, which offer more than one CAN Stop training group, so a further layer of nesting is not nescessary. We hypothesize that intervention groups show lower levels of cannabis use and higher levels of self-efficacy related to cannabis-abstinence after the intervention as compared to controls. To discover these effects, we calculated the needed sample size of n = 119, assuming a medium effect size of f = 0.25, given the power of the statistical test to .80 and setting the α-error on .05. Prior experience with the target group have shown that attrition rates among young cannabis users are rather high, so we calculated with an attrition rate of 50% when planning the number of nescessary participants at t0. With regard to further effects, we believe there are differences in the effectiveness of the training in the different settings. We hypothesize that the effect of the training (d) will be greater when less other interventions take place in the respective setting, that is, effects are bigger in juvenile prisons and out-patient institutions than in in-patient setting clinics.

Secondary analyses will be made to compare the clientele of the different settings. Here we assume that more aggravated and chronic cannabis users will be found in prisons and in-patient settings than in out-patient settings. As for the role forced access to the group (e.g. because of pressure from juidical institutions or teachers) plays, we believe no differences will be seen between participants, who indicated, they were attending the intervention group because of pressure from outside, as compared to participants, who decided to attend the group solely on their own accord. This is, because we assume the CAN Stop training itself is shaped in a way as to leave decisions about further consume open to participants, which inspires the internal motivation of all participants and therefore blurs differences regarding forced access to the training.

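### The single n = 119 fits the plan only as a trial total, so the stated power of .80 does not carry over to the separate comparisons within the four settings

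*Protocol article*

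**What the plan says.** The Background section of the protocol article explains that clientele and staff differ between settings and continues: "That is why the programme is implemented and evaluated separately in four different settings". Checking suitability by setting is the second goal, and drawing conclusions for implementation in the settings is the third.

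The Analysis section defines the effectiveness comparison as follows: "Comparisons will be made between intervention group and the TAU control group in the different settings using baseline controlled ANCOVAs". It then gives a general hypothesis of lower cannabis use and higher self-efficacy in intervention groups than in controls. One sample size comes next: "we calculated the needed sample size of n = 119, assuming a medium effect size of f = 0.25". The power is set at .80 and α at .05. For attrition the authors state: "we calculated with an attrition rate of 50% when planning the number of nescessary participants at t0". A hypothesis that the effect differs in size between settings follows, with no sample size or power of its own.

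The recruitment section says the target number of partners was derived from the power calculation, 50% attrition and groups of six to ten. It reports 11 partners in addiction aid and youth welfare and, for the other three settings, "9 cooperation partners of the out-patient medical system, 8 cooperation partners of the in-patient medical system and 3 participating prisons". The Analysis section adds: "There are no institutions, which offer more than one CAN Stop training group".

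**The concern.** The comparison is described by setting, but the sample size is a single number whose scope is not given. A reader who takes the two sentences together may conclude that each setting has 80% power for a medium effect. If 119 is the trial total, each setting has only a fraction of it.

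What is at stake is the reading of the setting results, which feed the second and third goals. Where power is low, a non-significant result is the likely outcome even if the planned effect is present. The plan expects larger effects in prisons and out-patient institutions than in in-patient clinics, yet the prison setting has by far the fewest partners.

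**Working it through.** **Inputs.** From the Analysis section: n = 119, f = 0.25 (d = 0.5 for two equal groups), power .80, α = .05, attrition 50%, no institution with more than one CAN Stop group. From the recruitment section: 11 + 9 + 8 + 3 = 31 partners and groups of six to ten. Assumed, because not stated: two-sided test, 1:1 allocation, recruitment proportional to partners, independent observations, and f = 0.25 already reflecting any gain from the baseline covariate.

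**The plan's own figure.** Power comes from the noncentral F distribution with 1 and N − 3 degrees of freedom (two groups, one covariate) and noncentrality λ = N × f². The smallest N with power .80 is 128 (λ = 128 × 0.0625 = 8.0). At N = 119, λ = 7.44 and power is 0.77. So 119 is not reproduced exactly. An unstated baseline correlation of about 0.25 to 0.3 would give 120 to 117. This is a separate matter, and the present point does not depend on it.

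**Total or per setting?**

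- As a total: 119 / (1 − 0.5) = 238 at t0, and 238 / 31 = 7.7 per partner, inside the range of six to ten.
- Per setting: 238 at t0 in each setting needs 238/10 = 23.8 to 238/6 = 39.7, so 24 to 40 partners per setting. The largest setting has 11.
- Per setting, counting only the CAN Stop half: 119 at t0 needs 119/10 = 11.9 to 119/6 = 19.8, so 12 to 20 institutions running a group. Even if all 11 partners in the largest setting ran one full group, there would be 110 places.

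Only the total reading agrees with the partner numbers.

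**Power within settings.** Shares of 119 are 119 × 11/31 = 42, 119 × 9/31 = 35, 119 × 8/31 = 31 and 119 × 3/31 = 12. Columns A to D show analysed N and power at f = 0.25.

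| Setting | A: share of 119 | B: 6 per partner, 50% lost | C: 10 per partner, 50% lost | D: most generous |
|---|---|---|---|---|
| Addiction aid and youth welfare | 42: 0.35 | 33: 0.29 | 55: 0.44 | 110: 0.74 |
| Out-patient | 35: 0.30 | 27: 0.24 | 45: 0.37 | 90: 0.65 |
| In-patient | 31: 0.27 | 24: 0.22 | 40: 0.34 | 80: 0.60 |
| Prison | 12: 0.12 | 9: 0.10 | 15: 0.15 | 30: 0.26 |

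Column D is ten per partner with no attrition or, equivalently, ten in each arm at every institution with 50% attrition (for example 11 × 20 × 0.5 = 110).

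**Detectable effect.** With the shares in column A, power .80 needs f of about 0.45, 0.49, 0.53 and 0.91, against 0.25 planned.

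**Clustering.** The plan itself expects variance shared within institutions. Allowing for it would lower every figure above. In the prison setting, where prisoners are not individually randomised, three institutions can give at best a comparison of two against one.

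**The case against.** The strongest reply is that the plan never claims .80 for each setting. The sentence just before the sample size is the general hypothesis of intervention against control, and the calculation can be read as serving that. Differences between settings come later, as further effects, with no power attached. A reader might infer that the article makes a false power statement for each setting. The documents do not support that: they leave the scope open, and the total reading is itself an inference from partner numbers. What remains is that the only comparison specified is by setting, no pooled test is named, and the figure stands next to it without a scope.

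A second reply is that the power figures depend on assumptions. This stands. The limit on group size applies to CAN Stop groups, and nothing caps the TAU numbers. Suppose 6, 5, 4 and 2 institutions run full groups of ten and half of the participants are analysed (30, 25, 20 and 10). With two controls for each of these, power is 0.60, 0.52, 0.44 and 0.24. If f = 0.25 is unadjusted and the baseline correlation is as high as 0.7, column A becomes 0.60, 0.52, 0.47 and 0.19. Combining that correlation with column D would take the three larger settings past .80, since the required N falls to about 128 × (1 − 0.49) = 65. That stacks favourable assumptions which the plan does not make. The figures are therefore a range, not a bound.

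A third reply is that null results in a setting need not be misread. A reader might infer that the authors will treat non-significance as ineffectiveness, but the article does not say so. It judges utility in the settings also from trainer feedback discussed with clinical experts. The misreading is a risk that the plan leaves open, not something it announces.

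Finally, details of the model may be in a full analysis plan that is not shown. The point does not rest on missing detail. It rests on the scope of a figure that the article does give.

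**Conclusion.** The point holds as a matter of scope. The article's own figures fit n = 119 only as a trial total, so the stated .80 does not apply to any comparison within a setting. Under 1:1 allocation, recruitment proportional to partners, independent observations and f = 0.25, power is about 0.35, 0.30, 0.27 and 0.12 for addiction aid and youth welfare, out-patient, in-patient and prison. For groups of six to ten after 50% attrition the range is about 0.10 to 0.44. No setting reaches .80 in the most generous case checked at f = 0.25, before any allowance for clustering.

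This should be fixed, but it does not invalidate the trial. The pooled comparison remains available, and the change is one of wording and emphasis.

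**What to change.** In the Analysis section:

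1. State that n = 119 and power .80 refer to the pooled comparison of intervention with TAU across settings, not to each setting. The authors should confirm that this was the intent.
2. Make one pooled nested ANCOVA, with setting as a fixed factor, the basis for the conclusion on effectiveness.
3. Report the four setting-specific comparisons as estimates with 95% confidence intervals. State that they are not separately powered, and give the power range together with its assumptions.
4. Add that a non-significant result in a setting is not evidence that the training is ineffective there.

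The cost is a few sentences and a less favourable power statement for the settings. No additional participants are needed for this change.

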### Measures

Young cannabis users participating at the study were asked to fill in several measures to assess target variables. Table 1 gives an overview of measures used.

**Table 1 T1:** Measures for young cannabis users

Target variable	Measure	Point of measurement
Sociodemographics Living situation Social network Problems with school, police, debts... Education Prior counselling and therapies		pre, follow-up
Screening for acute psychosis	Subscale of the Diagnostisches Interview psychischer Störungen (DIPS; Diagnostic Interview of psychiatric disorders) [26]	pre
Substance use history	Following the assessment standards III of the DG-Sucht (German Society for Addiction Research and Therapy)	pre, post, follow-up
Severity of dependence	Severity of dependence scale (SDS) [27]	pre, post, follow-up
Psychosocial adjustment	Youth self report (participants aged 14-17) [28] Young adult self report (Participants aged 18-21) [29]	pre, post, follow-up
Expected positive and negative effects of cannabis use	Comprehensive Cannabis Expectancy Questionnaire (CCEQ) [30]	pre, post, follow-up
Relationship to friends and peers	Questionnaire for health-related quality of life (Kiddo-KINDL revised, subscale "friends") [31]	pre, post, follow-up
Family relationships	Familienbogen/Selbstbeurteilungsbogen (family inventory, self-rating) [32]	pre
Motivation for change in cannabis use	Fragebogen zur Erfassung der Veränderungsbereitschaft (FEVER; Questionnaire to protocol the willingness for change) [33,34]	pre, post, follow-up
Personal goals with regard to changes in substance use	Zielskala [35]	pre, post, follow-up
Self-efficacy with regard to cannabis abstinence or limited cannabis use	Heidelberger Skalen zur Abstinenz-/Kontrollzuversicht (HEISA-16/HEIS-KOTZ-12; Heidelberg scales of confidence regarding abstinence/controlled use) [35]	pre, post, follow-up
Satisfaction with the training	Fragebogen zur Beurteilung der Behandlung, Version Patient (FBB-P; Questionnaire for the satisfaction with treatment, patient version) with minor adaptations [36]	post
Peer resistance regarding cannabis use	own development	pre, post, follow-up

In addition, trainers were asked to answer a short questionnaire about themselves prior to t0 in order to gather data for analysing possible trainer effects in secondary analyses. This included their professional background, own beliefs and attitudes towards cannabis use and personality characteristics, using the Big Five Inventory-10 (BFI-10) [25].

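### The self-efficacy ANCOVA adjusts for baseline cannabis use and not for baseline self-efficacy, which the trial already collects

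*Protocol article*

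**What the plan says.** The Analysis section of the protocol article compares intervention and treatment as usual in the different settings "using baseline controlled ANCOVAs", and completes the specification with "with cannabis use and abstinence-oriented self-efficacy as dependent variable and cannabis use at t0 as covariate". Two dependent variables are named and one covariate.

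Self-efficacy is not a minor endpoint. The Background and the Analysis section both pair it with cannabis use in the main hypothesis, and the Analysis section expects "higher levels of self-efficacy related to cannabis-abstinence after the intervention as compared to controls". The sample size is calculated for these two effects together.

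Table 1 in the Measures section has a row for "Self-efficacy with regard to cannabis abstinence or limited cannabis use" (HEISA-16 and HEIS-KOTZ-12), with measurement at pre, post and follow-up. Nowhere does the article bring the pre-training score into the model.

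**The concern.** An ANCOVA of a follow-up score usually takes the same measure at baseline as covariate, because that is normally the strongest single predictor of the later score. The cannabis-use model does this. The self-efficacy model, as written, takes the baseline of the other outcome.

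Two things are at stake. The first is precision: residual variance stays larger than the collected data require, so one of the two main tests has less power than it could have. The second is baseline imbalance. A difference between groups in self-efficacy at t0 is removed only to the extent that it runs parallel to cannabis use at t0.

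Imbalance is a realistic prospect in this design. The recruitment section says that prisoners cannot be randomised and that judicial placement decides their group, with only 3 prisons taking part. It also describes random assignment of cooperating institutions, of which the other three settings have 11, 9 and 8.

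**Working it through.** **The plan's own figure.** The Analysis section states "we calculated the needed sample size of n = 119". Its inputs are f = 0.25, 80% power and alpha 0.05. A two-group ANCOVA with one covariate (noncentral F, 1 numerator degree of freedom, noncentrality N × f²) needs N = 128 for 80% power at two-sided 0.05. At one-sided 0.05 it needs 101. With N = 119 the two-sided power is 0.77. So 119 is not reproduced. That is a separate matter and the present point does not depend on it; 119 is used below only as the stated sample size.

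**Inputs.**
- From the article: N = 119, f = 0.25 (d = 0.50 for two equal groups), alpha 0.05, taken as two-sided.
- Assumed, because the article gives no correlations: the correlation of post-training self-efficacy with cannabis use at t0 (r_use), 0.2 to 0.3, and with its own t0 score (r_own), 0.5 to 0.6. Wider ranges follow below.
- Simplifications: f = 0.25 is taken on the unadjusted scale, clustering by institution is ignored, and all 119 participants enter one comparison.

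**Residual variance.** With a single covariate, residual variance is proportional to 1 − r². Exchanging one covariate for the other changes it by the ratio (1 − r_own²)/(1 − r_use²):
- r_use = 0.3, r_own = 0.5: 0.75/0.91 = 0.82, a fall of 18%.
- r_use = 0.2, r_own = 0.6: 0.64/0.96 = 0.67, a fall of 33%.

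**Power.** The adjusted effect size is 0.25/√(1 − r²), so the noncentrality is 119 × 0.0625/(1 − r²) = 7.44/(1 − r²), with 119 − 3 = 116 denominator degrees of freedom.

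| Covariate | r | Noncentrality | Power at N = 119 | N for 80% power |
|---|---|---|---|---|
| Cannabis use at t0 | 0.2 | 7.75 | 0.79 | 123 |
| Cannabis use at t0 | 0.3 | 8.17 | 0.81 | 117 |
| Self-efficacy at t0 | 0.5 | 9.92 | 0.88 | 97 |
| Self-efficacy at t0 | 0.6 | 11.62 | 0.92 | 83 |

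**Wider range.** With r_own from 0.3 to 0.7 and r_use from 0 to 0.3, the variance ratio runs from 1.00 (0.3 against 0.3, no gain) to 0.51 (0.7 against 0). It exceeds 1 only if cannabis use predicts later self-efficacy better than the scale predicts itself. For example, r_own = 0.3 and r_use = 0.4 gives 0.91/0.84 = 1.08.

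**Both covariates together.** In an ordinary linear model, residual variation with both covariates cannot exceed that with cannabis use alone. The price is one denominator degree of freedom, 115 instead of 116. Adding the score, as opposed to exchanging covariates, therefore costs almost nothing even in the reversed case.

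**Imbalance, by illustration.** Suppose the groups differ by 0.3 SD in baseline self-efficacy that cannabis use does not explain, and the slope on later self-efficacy is 0.5 (both assumed). Then 0.3 × 0.5 = 0.15 SD stays in the estimated effect. Against d = 0.5 that is 0.15/0.5 = 30%, in either direction.

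**The case against.** The sentence announces baseline-controlled models in the plural, before both outcomes. The authors may mean that each outcome is controlled for its own baseline, with the covariate clause compressed, and a full analysis plan may say so. This reading is possible. But the article does not leave the covariate open: it names one, and for self-efficacy it names another variable. If the intention was different, the sentence still needs correcting; otherwise a later analysis with baseline self-efficacy would look like a change made after the fact.

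The imbalance argument depends on how allocation works. One part of the recruitment section assigns institutions; another has the hotline allocate individuals at random, except in prisons; and the Discussion treats cluster randomisation as a fallback. Under individual randomisation, chance imbalance adds variance but does not bias the estimator. This stands: the imbalance concern is firmest for prisons and otherwise conditional on allocation by institution. The loss of precision does not depend on it.

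The power figures are not the trial's power. They ignore the planned nesting and the comparisons by setting, they rest on assumed correlations, and they model an exchange of covariates while the remedy keeps both. All of this is true, and they should be read as illustration. It does not affect the direction, which holds whenever the scale predicts its own later score better than cannabis use does.

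Finally, Table 1 puts two instruments in one row, one for abstinence and one for controlled use, and the article does not say whether every participant completes both at each visit. If the form followed the participant's goal, a matching t0 score could be missing for some. This is an open question, not a demonstrated obstacle.

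**Conclusion.** The concern holds. Taken as written, the model for one of the two hypothesised effects omits that outcome's own baseline although it is measured, and adjusts for a different variable. Under the assumed correlations the omission costs about 7 to 13 percentage points of power at n = 119 (0.81 to 0.88 at the smallest, 0.79 to 0.92 at the largest). No gain from exchanging covariates is possible if the correlations are equal. Imbalance in baseline self-efficacy is left in the estimate except for the part shared with baseline cannabis use. Neither comparison is invalidated and the cannabis-use model is unaffected, so this is a change that should be made, not one on which the trial stands or falls.

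**What to change.** Replace the covariate clause in the Analysis section with a statement to this effect: each outcome is analysed with its own t0 value as covariate, within the planned nested model; the self-efficacy model uses the t0 score of the same scale, with cannabis use at t0 kept as a second covariate. The cannabis-use model stays as it is.

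The cost is one sentence and about one degree of freedom, with no new data, since Table 1 already schedules the scales before training. It is worth confirming at the same time that the scale analysed after training is completed by every participant at t0.

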## Discussion

In this paper, we describe the study design of an innovative training targeting young cannabis users in rather different settings, which are very differently organised but at the same time all share the goal to reduce their clientele's prior cannabis use. We are especially interested in how the different institutions will be able to implement the training, what the differences between their respective study participants are and how this is mirrored in the effect(s) of the training. A special difficulty of the study was to set up a study procedure which matches the different frameworks of the respective setting, starting at the professional background of the cooperation partners' staff, their legal and organizational background and their different interests.

Several difficulties may arise when it comes to the implementation of the study plan. First, it remains to be seen, whether it is suitable to use the centralized study telephone as a means to randomize young cannabis users into different institutions, especially, when they have already had contact to workers in one institution e.g. through a personal talk when handing out the study flyer, and they are assigned to another institution because the respective group is available only there. It remains to be seen, whether this potential switch marks a problem for recruitment, because other institutions are less easy to reach (e.g. with public transportation in rural areas) or an attachment has already been formed between one institution and a young cannabis user.

Another problem may arise through the referral of young cannabis users to other institutions by the centralized study hotline, because an institution, which may already have established a first contact to a young cannabis user, could "loose" a potential client to another, possibly competing institution and therefore may feel to loose money usually granted to them when treating the client. We hope that we can convince all cooperation partners that statistically, the possibility to "loose" clients through the centralized telephone hotline is as high as is the possibility to gain new clients because of the same centralized referral of study participants.

If it turns out, that the procedure with regard to the centralized telephone hotline poses a major threat to the recruitment of study participants, we will discuss to switch into a cluster randomized study design with cooperating institutions as randomized subjects.

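### The stated n = 119 does not follow from f = 0.25, power .80 and alpha .05 (128 are needed without covariate credit), and the stated inputs make no allowance for the institution clustering that the analysis plans to model

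*Protocol article*

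**What the plan says.** The Analysis section of the protocol article gives the sample size in one sentence: "we calculated the needed sample size of n = 119, assuming a medium effect size of f = 0.25". The same sentence fixes power at .80 and alpha at .05. The section then mentions 50% attrition as a separate allowance for the number needed at t0.

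The test is described just before. The contrast is CAN Stop against treatment as usual across the settings, and the model is given as follows: "using baseline controlled ANCOVAs with cannabis use and abstinence-oriented self-efficacy as dependent variable and cannabis use at t0 as covariate". The section also commits to a clustered analysis: "We plan to perform nested analyses in order to handle the variance, which is shared between participants attending the same institution". It gives no ICC, design effect, baseline correlation or sidedness, and does not say whether 119 is a total, a number per group or a number per setting.

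The recruitment section says that the target number of cooperating institutions was worked out from a power calculation, the 50% attrition and training groups of six to ten. It reports "a total of 11 cooperation partners within the youth welfare and drug addiction aid, 9 cooperation partners of the out-patient medical system", plus 8 in-patient partners and 3 prisons. On allocation it says "Participating cooperation partners were randomly assigned to perform the CAN Stop intervention plus their usual treatment as an intervention group"; the remaining partners supply control participants. It also says that a telephone hotline randomly allocates individual users to intervention or wait-list groups at the respective institutions, prisons excepted. The Discussion adds that, if the hotline fails, "we will discuss to switch into a cluster randomized study design with cooperating institutions as randomized subjects".

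**The concern.** Two things do not fit. First, a medium effect of f = 0.25 in a two-group comparison at these error rates is a standard calculation, and its answer is not 119. Second, the calculation and the planned analysis disagree: the analysis lets participants at one institution share variance, while the calculation shows no allowance for it. Because 119 lies below the minimum for independent data, no clustering inflation can be hidden in it unless an unstated gain from elsewhere offsets it.

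Two uses of the number are at stake. The recruitment target for institutions was built on the power calculation. And a null result would be read against a claimed 80% power that the stated inputs do not support.

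**Working it through.** **Inputs from the article.** N = 119, read here as the total for one two-group comparison; f = 0.25, which is d = 2f = 0.5 for two equal groups; alpha .05; target power .80; institutions 11 + 9 + 8 + 3 = 31; attrition 50%.

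**Assumptions, not in the article.** 1:1 allocation, two-sided test, ICC between 0 and 0.10, baseline–outcome correlation r of 0, 0.27 or 0.5.

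**Step 1: try to reproduce 119.** Two-group ANCOVA with one covariate: noncentral F with df1 = 1, df2 = N − 3, noncentrality λ = N f².

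- N = 119: λ = 119 × 0.0625 = 7.44, power 0.772.
- N = 128: λ = 128 × 0.0625 = 8.00, power 0.801. N = 127 gives 0.798, so 128 is the minimum.
- The effect detectable with power .80 at N = 119 is f ≈ 0.259.
- With 50% attrition, 119 / 0.5 = 238 at t0 and 128 / 0.5 = 256.

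Other simple set-ups at f = 0.25 also miss 119: one-sided t test, 101; three groups, 158; four groups or a 2 × 4 interaction, 179. Two four-group repeated-measures set-ups come close (118 and 121), but they need a correlation that is not stated and are not the analysis described.

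A total of 119 does come out if one input changes: f = 0.26, target power 0.77, or f = 0.25 taken as the unadjusted effect with r ≈ 0.27. In the last case the adjusted effect is 0.25 / √(1 − 0.27²) = 0.260.

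**Step 2: does clustering apply?** Institutions were assigned to one condition. The section on measures against bias says that control institutions' trainers are trained only after t1. The Discussion describes users being sent elsewhere because the group exists only there. So each institution appears to deliver one condition up to t1, and variance between institutions enters the treatment contrast even where individuals were allocated by hotline.

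**Step 3: size, conditional on assumptions.** Take 119 completers over 31 institutions, so m = 119 / 31 = 3.84. Then:

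- design effect DE = 1 + (m − 1) × ICC
- effective N = 119 / DE
- noncentrality = [0.5 / √(1 − r²)] × √(effective N) / 2
- noncentral t with 31 − 2 = 29 df, critical value 2.045

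Example at ICC 0.05, r = 0: DE = 1 + 2.84 × 0.05 = 1.142; effective N = 104.2; noncentrality = 0.5 × 10.21 / 2 = 2.55; power 0.69.

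| Assumed ICC | DE | Effective N | Power, r = 0 | Power, r = 0.27 | Power, r = 0.5 |
|---|---|---|---|---|---|
| 0 | 1.000 | 119.0 | 0.75 | 0.78 | 0.86 |
| 0.02 | 1.057 | 112.6 | 0.73 | 0.76 | 0.84 |
| 0.05 | 1.142 | 104.2 | 0.69 | 0.73 | 0.81 |
| 0.10 | 1.284 | 92.7 | 0.64 | 0.68 | 0.77 |

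With 31 institutions, 29 df and no covariate credit, power .80 would need about 145, 164 and 214 completers at ICC 0.02, 0.05 and 0.10.

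**The case against.** The strongest reply is that the planned covariate was left out of the 128. If f = 0.25 is the unadjusted effect, a correlation of only about 0.27 gives 119, and a correlation of 0.5 keeps power above .80 up to an ICC of 0.05. This stands as far as it goes: the article does not say whether f is before or after adjustment. But then the credit is an unstated input on which the whole figure depends, and at r = 0.27 it is used up before any clustering is counted. Cannabis use at t0 is also the covariate for self-efficacy, where the relevant correlation is a different one.

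Second, the unit behind 119 is open. If it is per group, power with 238 independent participants is 0.97. If it is per setting, each institution would hold more participants and the loss from clustering would grow. That also stands, and it is a reason to define the number.

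Third, a condensed article may leave the ICC and similar details to a fuller document. Agreed: their absence alone would be no finding. The point is that the stated number does not follow from the stated inputs.

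Two stronger readings are tempting. A reader might infer that the trial's true power is 0.64 to 0.75. The documents do not support that, since the range needs an assumed ICC, no covariate gain and 119 as the overall total. A reader might also infer that this is already a plain cluster-randomised trial with arm fully confounded with institution. The article also describes individual allocation by hotline outside prisons, which should reduce clustering from pre-existing client differences, and there are several institutions per arm. What remains is institution, trainer and group variance.

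**Conclusion.** The point holds in this form: 119 is not the sample size for the two-group comparison at f = 0.25, power .80 and alpha .05, and the stated inputs carry no allowance for the nesting that the analysis plans to model.

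The part that needs no ICC is modest. Reading 119 as a total, with equal groups, a two-sided test and no covariate credit, the gap is 9 completers (18 at t0 after 50% attrition), or about 3 points of power. The clustering part is conditional. Under the assumptions tabulated, power at 119 runs from 0.64 to 0.86, below or above the target depending on two quantities that the article does not give. No single value within that range can be called the trial's power.

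**What to change.** In the Analysis section:

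- Say whether 119 is a total, per group or per setting, and whether it counts completers.
- Replace the sample-size sentence with a calculation for the planned nested ANCOVA. State the two-group test and its sidedness, the assumed ICC, completers per institution, institution-level degrees of freedom, and any baseline correlation credited, for each of the two outcomes.
- Restate the power at 119, or the smallest detectable effect, as a range over plausible ICC and baseline correlation, marked as assumptions.
- Use the same calculation if the cluster-randomised fallback in the Discussion is adopted.

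The cost is wording and probably a less favourable stated power. No extra enrolment is asked for.
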